**Methods:**

We will use the Replicating Effective Programs (REP) implementation strategy to support CTI implementation at 32 sites selected by our partners. Half (*n*=16) of these sites will also receive 9 months of external facilitation (EF, enhanced REP). We will conduct a type 3 hybrid cluster-randomized trial to compare the impacts of REP versus enhanced REP. We will cluster potential sites into three implementation cohorts staggered in 9-month intervals. Within each cohort, we will use permuted block randomization to balance key site characteristics among sites receiving REP versus enhanced REP; sites will not be blinded to their assigned strategy. We will use mixed methods to assess the impacts of the implementation strategies. As fidelity to CTI influences its effectiveness, fidelity to CTI is our primary outcome, followed by sustainment, quality metrics, and costs. We hypothesize that enhanced REP will have higher costs than REP alone, but will result in stronger CTI fidelity, sustainment, and quality metrics, leading to a business case for enhanced REP. This work will lead to products that will support our partners in spreading and sustaining CTI in aftercare.

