### Implementation strategy: enhanced REP

In addition to REP, 16 of 32 aftercare sites will receive EF (enhanced REP), which will provide these sites with support tailored to their local contexts. Compared to REP alone, REP enhanced with EF is a higher intensity and higher cost strategy to support CTI implementation. Figure 4 depicts REP versus enhanced REP activities as experienced by sites. We hypothesize that enhancing REP with EF will improve CTI fidelity and sustainment by catalyzing case management activation and organizational changes.

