### CTI fidelity

We will measure site-level CTI fidelity 12 months after REP initiation, capturing adherence to CTI’s core components in the 6 months prior to measurement. We will employ methods adapted from a study of CTI for homeless adults leaving shelters [22] and developed with experts who have measured CTI fidelity across RCTs [22, 26]. Fidelity assessors will use a roster of HEVs engaged at implementation sites to randomly select 5 HEVs (“exemplars”) on each case manager’s caseload. Videoconferences with each case manager will be used to complete a templated review form by reviewing charts from these exemplars. Data from the exemplar review template will be used by the fidelity assessors to complete and score an adapted version of the CTI Implementation Self-Assessment Tool [27], which has cut-offs for adequate versus inadequate fidelity. We will use the *t*-test to compare fidelity between sites receiving REP versus enhanced REP.

These scores will be integrated with analyses of semi-structured aftercare staff interviews at 12 months and periodic reflections; qualitative data will glean staff perceptions of CTI fidelity. Within and across implementation strategies, we will compare sites with quantitative scores indicating adequate versus inadequate fidelity and use targeted coding of qualitative data to explore contextual factors associated with fidelity ratings.

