### Housing stability and hospitalizations

We will assess housing stability and hospitalizations among HEVs during and after receiving aftercare services, comparing: (a) REP versus enhanced REP sites and (b) the 32 implementation sites with a control group of 32 sites that did not implement CTI, matched on geographic setting and number of case managers. We will use administrative data (from VA’s Corporate Data Warehouse [CDW] and homeless registry) to assess these outcomes (Table 3).

**Table 3 Tab3:** Summary of quality metrics assessed using VA administrative data

Domain	Quality metric
Housing stability	• Number of days between aftercare entry and first VA indicator of housing instability^a^ • Annual number of encounters with VA homeless services • Annual number of discrete episodes^b^ of engagement with VA homeless services
Hospitalizations	• Number of days between aftercare entry and first hospitalization (VA or non-VA) • Annual number of hospitalizations (total and separated into medical/surgical versus mental health) • Annual number of hospital bed days
Outpatient service use	• Primary care provider assignment (yes/no) • Presence or absence of at least one primary care visits/year • Use of VA vocational services (among HEVs seeking employment) • Total number of mental health visits (among HEVs with mental health disorders) • Total number of substance use disorder treatment visits (among HEVs with substance use disorders)

^a^Use of VA homeless services

^b^New episodes desfined by 30 days passing between encounters

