For all HEVs who enter implementation and control sites between 6 and 18 months post-implementation (the time during which we have captured fidelity), we will determine the number of days between aftercare entry and the first VA indicator of housing instability (i.e., homeless service use). Within each cohort, for sites that receive REP or enhanced REP to support CTI implementation, we will use survival analysis (Cox proportional hazards models) to compare time to the first presence of a housing instability indicator among those who received aftercare in the same period in matched control sites. Models will use clustered robust standard errors to account for potential within-site correlation. We estimate that there will be 4,080 HEVs split evenly between implementation and control sites (~64 HEVs/site). Using a two-sided alpha level of 0.05, we estimate having 80% power to detect a 25% relative difference in time to housing instability indicators. This estimate is based on a log-rank test, assuming an intraclass correlation within each site of ~0.05.

Within implementation sites, we will assess for independent associations between housing instability among HEVs and sites’ assigned implementation strategy (REP versus enhanced REP) and CTI fidelity. We will also compare HEVs between implementation and control sites; per HEV, we will compare the annual number of encounters with VA homeless services (a proxy for service intensity needed) and the annual number of episodes of homeless service engagement (with new episodes defined by ≥30 days between encounters). Comparisons will be made using negative binomial regression models with clustered robust standard errors for site-level clustering.

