Similarly, we will determine, for each HEV, the days between entry into aftercare and hospitalization (at the VA or paid for by VA at an outside hospital) and describe the time to hospitalization using Kaplan-Meier curves. We will include all hospitalization types (mental health, medical/surgical), analyzing the time to any hospitalization and by type. We will also assess for independent associations between these outcomes and implementation strategy and CTI fidelity using Cox proportional hazards models. Additional secondary outcomes will be the annual number of hospitalizations (total and by type) and the number of bed days per HEV. We will also assess time trends in housing stability and hospitalizations within implementation sites, comparing pre- and post-implementation.

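### As described, the REP versus enhanced REP analyses of housing instability and hospitalization appear to adjust the randomized strategy effect for CTI fidelity, which is measured after randomization and lies on the hypothesized causal path

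*Protocol article*

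**What the plan says.** All references are to the protocol article.

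- *Housing stability and hospitalizations* sets out two contrasts: "comparing: (a) REP versus enhanced REP sites and (b) the 32 implementation sites with a control group of 32 sites that did not implement CTI". No model is attached to contrast (a) at that point.
- The same section describes the strategy analysis for housing instability, which uses the implementation sites only: "we will assess for independent associations between housing instability among HEVs and sites’ assigned implementation strategy (REP versus enhanced REP) and CTI fidelity".
- For time to hospitalization it says: "We will also assess for independent associations between these outcomes and implementation strategy and CTI fidelity using Cox proportional hazards models".
- The other models for housing concern the control sites. The first Cox model is written to "compare time to the first presence of a housing instability indicator among those who received aftercare in the same period in matched control sites". The negative binomial models are introduced with "We will also compare HEVs between implementation and control sites; per HEV, we will compare the annual number of encounters with VA homeless services".
- *CTI fidelity* fixes the timing: "We will measure site-level CTI fidelity 12 months after REP initiation, capturing adherence to CTI’s core components in the 6 months prior to measurement". *CTI sustainment* repeats the assessment at 18 months.
- *Implementation strategy: enhanced REP* gives the first link of the pathway: "We hypothesize that enhancing REP with EF will improve CTI fidelity and sustainment by catalyzing case management activation and organizational changes".
- The Methods paragraph of the Abstract gives the second: "As fidelity to CTI influences its effectiveness, fidelity to CTI is our primary outcome".

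**The concern.** Randomization protects the comparison of sites by assigned strategy. It does not protect a comparison of sites by strategy at a given level of fidelity, because fidelity arises after assignment and may itself be changed by it. Holding fidelity fixed removes whatever part of the strategy effect passes through fidelity, which is the route the protocol expects. It also opens a second problem. Fidelity is not randomized, so site factors that affect both fidelity and veterans' outcomes no longer cancel between arms. Staff turnover, which the Discussion names as a challenge, is a plausible example.

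There is a smaller timing issue. The veterans analysed enter at months 6 to 18, while the 12-month fidelity score describes months 6 to 12. For those who enter in months 6 to 12, the fidelity window overlaps their follow-up, so exposure does not clearly precede outcome.

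What is at stake is how the secondary comparison is interpreted. The overall hypothesis is that enhanced REP gives better quality metrics, and Table 5 lists housing stability among the non-financial benefits in the business case. If facilitation works as theorized, a fidelity-adjusted coefficient could understate that benefit and be misread as the effect of assignment.

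**Working it through.** **1. The plan's own figure.** The article states 80% power for a 25% relative difference, with 4,080 veterans and an intraclass correlation of about 0.05. That figure concerns implementation versus control sites.
- Veterans per site: 4,080 / 64 = 63.75.
- Design effect: 1 + (63.75 − 1) × 0.05 = 4.14. Effective sample: 4,080 / 4.1375 = 986.
- At a hazard ratio of 0.75, 80% power needs 380 events (Schoenfeld) or 385 (Freedman), about 39% of 986.
- No event proportion is given, so the 80% can be neither confirmed nor refuted. No power figure is given for REP versus enhanced REP, and this point does not depend on one.

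**2. Which analyses address REP versus enhanced REP?** For these outcomes, the first Cox model and the negative binomial models name control sites as the comparator. That leaves the two sentences that pair assigned strategy with fidelity.

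**3. What would a model with both terms estimate?** Work on the site-level log-hazard scale, with 16 versus 16 sites. Let *a* be the shift in fidelity due to enhanced REP (in SD), *b* the log hazard ratio per SD of fidelity, and *d* the direct strategy effect.
- Total effect of assignment: *d* + *ab*.
- Strategy coefficient with fidelity in the model and no confounding: *d*.

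Assume a total hazard ratio of 0.75, so *d* + *ab* = ln 0.75 = −0.288. If a share *s* is mediated, *d* = (1 − *s*)(−0.288):
- *s* = 0: exp(−0.288) = 0.75
- *s* = 0.5: exp(−0.144) = 0.87
- *s* = 1: exp(0) = 1.00

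**4. Add confounding.** Assume a site factor correlated 0.5 with fidelity within arm that changes the log hazard by ±0.2 per SD. The fidelity slope is then biased by 0.5 × (±0.2) = ±0.1, and the strategy coefficient becomes *d* ∓ 0.1*a*. With *a* = 1:
- *s* = 0: exp(−0.288 ± 0.1) = 0.68 to 0.83
- *s* = 0.5: exp(−0.144 ± 0.1) = 0.78 to 0.96
- *s* = 1: exp(± 0.1) = 0.905 to 1.105

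A simulation of 20,000 replicates per scenario, with *a* at 0.5, 0.8 and 1.0, agrees. Its ranges are 0.68–0.83, 0.78–0.96 and 0.91–1.11. The estimate without fidelity stayed at about 0.75 in every scenario.

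The total effect, *a*, the mediated shares and the confounding strengths are all assumptions; the documents give none of them.

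**The case against.** The strongest reply is that joint entry is inferred. No sentence specifies one model containing both terms. The section announces a plain comparison by strategy, and the evaluation overview likewise promises quality metrics compared between the two strategies, without mentioning fidelity. The hospitalization sentence opens as an addition to other analyses. A condensed article may leave the model for contrast (a) to an analysis plan that is not shown. This stands in part: a reader might infer that no strategy-only analysis will be done, and the article does not establish that. What remains is that the analysis actually described for this contrast is, on its ordinary meaning, a mutually adjusted one.

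Three other stronger readings should be resisted.

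- **The bias must be toward the null.** That is the expected direction under the protocol's own pathway, but confounding can push the coefficient away from the null (0.68) or past it (1.11).
- **The model would report no effect.** That needs full mediation. The protocol never says fidelity is the only route, and Table 2 lists facilitation activities that could act outside it, such as feeding back veterans' service use to staff.
- **The business case rests on this coefficient.** The cost and return-on-investment models compare the arms with no fidelity term mentioned, and the business case combines cost offsets with several non-financial benefits.

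On timing, the 18-month reassessment means the fidelity data are not limited to months 6 to 12, so the overlap is a lesser point.

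**Conclusion.** The point holds in a limited form. For housing instability and hospitalization, the only REP versus enhanced REP analyses described pair assigned strategy with fidelity. On the ordinary reading they adjust the randomized effect for a post-randomization variable that the protocol itself places on the causal path. The resulting coefficient is at best a direct effect, and even that requires no unmeasured confounding of fidelity and outcome. It does not answer contrast (a).

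The size cannot be fixed from the documents. If the true hazard ratio for assignment were 0.75, the adjusted value would be 0.87 at half mediation and 1.00 at full mediation without confounding, and between 0.68 and 1.11 across the confounded scenarios. The primary t-test on fidelity, the randomization and the data collection are untouched. This is a moderate issue confined to secondary outcomes.

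**What to change.** In *Housing stability and hospitalizations*, for both outcomes:

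- State that the REP versus enhanced REP effect is estimated by assigned strategy, adjusted for cohort and the stratification factors (geographic setting and number of case managers), with site-clustered standard errors and without fidelity.
- Report associations between fidelity and outcome in a separate model, labelled observational.
- Label any model with both strategy and fidelity as exploratory mediation, and do not present its strategy coefficient as the effect of assignment.
- Optionally, add a sensitivity analysis of the fidelity association limited to veterans entering at months 12 to 18, so that the 12-month score precedes the outcome. This drops those entering at months 6 to 12 and so loses precision.

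The cost is revised wording and one extra model per outcome. No new data are needed.

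### The planned pre-implementation site outcomes could sharpen the REP versus enhanced REP comparison of housing stability and hospitalization, but the article names no such baseline term in those models

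*Protocol article*

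**What the plan says.** All of this stands in the protocol article, mainly under Housing stability and hospitalizations.

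- **Pre-implementation data.** The one stated use is: "We will also assess time trends in housing stability and hospitalizations within implementation sites, comparing pre- and post-implementation".
- **Randomized contrast, housing instability.** Independent associations are to be assessed with sites' "assigned implementation strategy (REP versus enhanced REP) and CTI fidelity".
- **Randomized contrast, hospitalization.** The plan is to assess "independent associations between these outcomes and implementation strategy and CTI fidelity using Cox proportional hazards models".
- **Power.** For implementation versus control sites, "we estimate having 80% power to detect a 25% relative difference in time to housing instability indicators". The basis is 4,080 HEVs, about 64 per site, and: "This estimate is based on a log-rank test, assuming an intraclass correlation within each site of ~0.05". No power is stated for REP versus enhanced REP.
- **Number of sites.** Participating sites and the Discussion both say that the funder set the 32 sites. The Discussion adds that the number did not come from a power analysis.
- **Balance.** Under Study design, sites are randomized within cohort in permuted blocks, stratified by geographic setting and number of case managers.
- **Rank.** The Abstract makes CTI fidelity the primary outcome and places quality metrics after it.

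**The concern.** Whether enhanced REP improves housing stability and hospitalization over REP is part of Aim 2 and feeds the business case. Only 16 versus 16 sites bear on it. In a trial with few sites and many clients per site, adding clients helps little, because stable differences between sites make up most of the error. A site's own earlier level of the same outcome is the natural predictor of those differences, and the plan will already hold it.

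If the baseline stays out of the randomized comparison, persistent site differences remain in the error term. A chance imbalance in prior site performance also goes unadjusted, because prior outcome level is not a stratification factor. The stake is precision. Randomization keeps the unadjusted comparison valid.

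**Working it through.** **Inputs from the article.** Two-sided alpha 0.05; 80% power; 25% relative difference; log-rank test; intraclass correlation about 0.05; 4,080 HEVs in 64 sites (4,080/64 = 63.75 per site); 16 versus 16 randomized sites.

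**Inputs assumed, because the article does not give them.** Pre/post correlation of true site effects, r = 0 to 0.8. Pre-period HEVs per site, m0 = 16 to 64. The article's 64 per site refers to people entering 6 to 18 months after implementation, not to a pre-period.

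**Step 1: the plan's own figure.** Design effect = 1 + (63.75 − 1) × 0.05 = 4.14. Effective sample = 4,080/4.14 ≈ 986. Reading the 25% difference as a hazard ratio of 0.75, the events needed (Schoenfeld) are 4 × (1.960 + 0.842)²/(ln 0.75)² ≈ 380, an event proportion of 380/986 ≈ 0.385. Read as 1.25, 631 events are needed, about 64%. No event proportion is given, so the 80% cannot be fully reproduced. Both values are attainable, so nothing shows it to be wrong, and it is taken as given.

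**Step 2: the randomized contrast.** Noncentrality with 64 sites = 1.960 + 0.842 = 2.802. With 32 sites it is 2.802/√2 = 1.981. Power = Φ(1.981 − 1.960) ≈ 51%, or 48% with a t reference on 30 degrees of freedom. Once the 80% is accepted, this step needs no event proportion. If it is not accepted, power at a hazard ratio of 0.75 runs from 30% to 82% as the event proportion goes from 0.2 to 0.8.

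**Step 3: between-site share.** Reliability of one period's site mean = 64 × 0.05/(1 + 63 × 0.05) = 3.2/4.15 = 0.77. This is an upper bound on what a baseline could remove. It would be reached only if site effects were perfectly stable and the baseline were measured without error.

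**Step 4: what a real baseline removes.** Reliability of the pre-period site mean, R0 = m0 × 0.05/(1 + (m0 − 1) × 0.05), is 0.46, 0.63 and 0.77 for m0 = 16, 32 and 64. The cut in variance is r² × R0 × 0.77, and the noncentrality becomes 1.981/√(1 − cut). For example, r = 0.5 and m0 = 64 give a cut of 0.25 × 0.771 × 0.771 = 0.149, noncentrality 1.981/√0.851 = 2.147 and power Φ(0.187) ≈ 57%.

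| r | Variance cut, m0 = 16 to 64 | Power, normal approximation (51% unadjusted) | Gain with t reference, simulated (about 48% unadjusted) |
|---|---|---|---|
| 0 | 0% | 51% | about −1 point |
| 0.3 | 3–5% | 52–53% | about 0 |
| 0.5 | 9–15% | 55–57% | 2–5 points |
| 0.7 | 17–29% | 59–65% | 7–12 points |
| 0.8 | 23–38% | 62–71% | 9–19 points |

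**Step 5: small-sample check.** The last column comes from simulated site means, 16 versus 16, analyzed by least squares with and without the baseline; the gains are good to about a point. They are smaller than the normal approximation suggests because, with 32 sites, the covariate costs a degree of freedom and its chance correlation with arm adds variance. The last column is the one to rely on.

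**The case against.** The strongest objection is that the point is read from silence. A reader might infer that the plan excludes baseline adjustment, or reserves the pre-implementation data for the trend alone. The article does not say so. It gives no covariate list for any model, its wording about independent associations suggests multivariable models, and covariate sets are commonly left to an analysis plan, which is not shown. This stands. The supportable statement is that no site baseline is named, while another use of the same data is.

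A reader might also infer that the pre/post trend cannot compare the strategies. The sentence names no such contrast, but all 32 implementation sites are randomized and nothing says that the trend will be pooled over strategy.

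On size, the inputs that decide the gain are absent from the article. Pre- and post-period HEVs are largely different people, the entry window opens 6 months after implementation, and the Discussion acknowledges high staff turnover. A weak correlation is therefore plausible, and the gain would then be nil. The stratification factors may also already account for some of the between-site variance. All of this stands, which is why the result is a range that starts at a small loss.

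Finally, the calculation uses a linear comparison of site means, whereas the plan uses Cox and negative binomial models with clustered robust errors. The figures are approximations, and covariate adjustment in a Cox model can change the hazard ratio being estimated.

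What remains is that the data are already planned, the cost is about a point of power, and a choice to adjust made after outcomes are seen would be less credible.

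**Conclusion.** The point holds as a modest efficiency improvement for secondary quality metrics. It is not an error, a contradiction or a false power claim: the 80% belongs to the implementation versus control comparison, and the article openly says that the number of sites was not power-based. CTI fidelity, the primary outcome, is unaffected.

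If the stated 80% is accepted, REP versus enhanced REP has about 48–51% power for the same 25% difference. The gain becomes clear only at a pre/post site correlation of around 0.7 or more. The ranges rest on assumed correlations and pre-period caseloads and on a site-mean approximation to the planned models.

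**What to change.** In the Cox and negative binomial models for REP versus enhanced REP, prespecify the site's pre-implementation level of the same outcome as a site-level covariate. This would be the event rate or mean count among HEVs entering in a fixed window before the cohort's start, with follow-up for this covariate ending at that start so that assigned strategy cannot affect it.

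An alternative is to fit pre- and post-implementation HEVs in one model and report the strategy-by-period term. Its estimand is not identical to that of the covariate model, so the plan should say which of the two is the main analysis. Keep the pre/post trend within implementation sites as descriptive.

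If an analysis plan already contains such a term, a sentence pointing to it is enough. Otherwise the cost is analysis wording and one site-level degree of freedom, about 1 point of power if the correlation is zero. The data are already to be obtained for the trend analysis.
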